### Step 5: Feedback and data use

If electronic data collection tools are used, data will be entered and cleaned during field work. If paper data collection forms are used, following field work data entry will be completed in Angola. Data analysis will subsequently be conducted by both the implementing partner in Angola and UNC. Stakeholders in HIV/AIDS prevention and control activities in each province will be invited to participate in a workshop presentation of the results and to discuss the priority action plan based on the sites / people at risk identified. A data use workshop will be conducted to train Ministry of Health and other organization implementing HIV prevention programs for key populations in programmatic planning based on mapping and survey data.

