### C. Population Size Estimate Analysis

#### Population Size Estimation Analysis using PLACE

1. For each area that was mapped, we will estimate the number of sites in each area by type of site and type of key population at site
2. We will estimate the number of each type of key population at each type of site
3. We will provide a map of sites indicating the number of key populations at each
4. We will estimate the total number of key population member in each zone and in the sub-national areas included in the estimate
5. We will extrapolate the estimate to include areas not covered
6. We will estimate the number of key populations missing from the estimate based on findings from formative research
7. We will refine the size estimates based on mobility of key populations, visits to multiple venues, and variety in frequency of attendance
8. We will use the size estimates to calculate coverage for components of the comprehensive program for key populations

The following steps for size estimation will be followed:

1. Review data to confirm completeness of site lists and adequacy of estimates of the number of key population members at each site. Check the quality of the data by comparing the number of sites named and the number of times each was named with the number of reports naming a site from community informants. Check that there are sites named in every area included in the mapping activity. Confirm that the interviewers included members of each key population and that targets for type and number of community informants were reached. Review the list of sites that were not located and re-visit a random sample to confirm that the sites do not exist.
2. Calculate a point estimate for the number of each key population at each site based on the reported range provided. At each site, informants will be asked to estimate the maximum and minimum number of key populations at the site at a busy time.
3. Separate the estimates from sites that were initially identified as sites with key populations from sites that were not reported to have key populations. The rationale for treating the two types of sites differently is that they are sampled with different sampling fractions and the expected number of key populations at the sites reported to have key populations will be higher than at the other sites.
4. Add up the median number of key populations at each site for an initial crude estimate of the size of each population.

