5. Produce a map illustrating number of key populations at each site using the median for the size estimate.
6. Adjust estimates based on information about frequency of visiting sites, frequency of visiting more than one site in a day, and the percentage of sites that have key populations but were not initially identified as sites with key populations.
7. Use the formula below to estimate the size based on the key population sites and separately for the other sites. The formula is:

$$E_i = s_i(1-p_i) + (s_i * p_i / m_i)$$

$E_i$  = the estimated key population members in an area

$s_i$  = estimate at the site level

$p_i$  = Proportion of female sex workers solicit in two or more sites

$m_i$  = Mean number of places a female sex worker solicit

For example,

If  $s_i$  from all the key population sites is 10,000 and 10% solicit in other sites, and the mean number of places the 10% solicit is 2 then the estimate is

$$10,000 (1 - 0.1) + (10,000 * 0.1 / 2)$$

$$= 9000 + 10,000 * 0.05$$

$$= 9000 + 500$$

$$= 9500$$

The formula is reasonable because it counts all of who are only at one place and for the ones who go to more places, the percentage of that group is reduced because the people might have counted at more than one place. This could be repeated for key populations at Other Sites. If 500 were found at Other Sites, the estimate would be 10,000.

8. Use the area estimates to develop national estimates. National estimates are developed by extrapolation of data. One approach is to estimate the percentage of the male and female population who is a member of a key population in the areas where the mapping and size estimation activity was done. Apply the percentage estimated in one area to the areas that are similar.
9. Meet with stakeholders to review the estimates and ensure that the size estimates are reasonable and acceptable to the stakeholders.
10. The size estimates can be used as the denominator in coverage estimates. If the randomly selected members of the key population were asked questions about access to testing and other prevention initiatives, additional analysis of their responses would be useful.

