Size estimates of populations at risk for HIV/AIDS infection help policy makers and program administrators understand the scope of the HIV problem, plan appropriate interventions, and allocate sufficient resources. Population size estimates will be used as denominators in calculating program coverage and producing estimates and projections of the HIV epidemic in areas where calculated. The data are intended to be used by the MoH, non-governmental organizations (NGOs), and other stakeholders for disease control purposes, specifically for program coverage planning and assessments.

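### Step 9 of the PLACE size estimation makes stakeholder acceptability a condition on the estimate, with no rule limiting changes or requiring the data-based figure to be reported

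*Protocol*

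**What the plan says.** The procedure is in Protocol section VIII.C, *Population Size Estimation Analysis using PLACE*, which has a list of eight analyses followed by ten working steps.

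- Steps 1 to 8 check the site lists, derive a number per site, separate the two kinds of site, sum and map the numbers, adjust for people who use several sites, and extrapolate.
- Step 9 reads: "Meet with stakeholders to review the estimates and ensure that the size estimates are reasonable and acceptable to the stakeholders".
- Step 10 begins: "The size estimates can be used as the denominator in coverage estimates".
- Item 8 of the first list gives the same use: "We will use the size estimates to calculate coverage for components of the comprehensive program for key populations". The closing paragraph states it more firmly: "Population size estimates will be used as denominators in calculating program coverage". That paragraph also names estimates and projections of the epidemic as a use.

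On the users of the figures, the closing paragraph says: "The data are intended to be used by the MoH, non-governmental organizations (NGOs), and other stakeholders for disease control purposes". For the results workshop, section VI.C, Step 5, says: "Stakeholders in HIV/AIDS prevention and control activities in each province will be invited".

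**The concern.** A meeting at which informed people test an estimate for plausibility is normal practice and is not the difficulty. The difficulty is the instruction to *ensure* that the estimate is acceptable. That sets a condition on the value of the result after the data have produced it and just before it may be used. The partner condition, *reasonable*, has no range or definition attached, so it does not limit the outcome either.

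If an estimate were altered to meet this condition and only the altered figure were reported, a reader could not separate what the site data gave from what was agreed in the meeting. The size estimate is itself an output, a denominator for coverage and an input to epidemic projections, so an untraced change would carry into each of these.

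**Working it through.** **1. The section's own figure.** The worked example starts from a site total that "is 10,000 and 10% solicit in other sites, and the mean number of places the 10% solicit is 2 then the estimate is" (the protocol then gives the result). With s = 10,000, p = 0.10 and m = 2:

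E = s(1 − p) + s·p/m = 10,000 × 0.90 + 10,000 × 0.10 / 2 = 9,000 + 500 = 9,500.

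The text continues: "If 500 were found at Other Sites, the estimate would be 10,000". Check: 9,500 + 500 = 10,000. Both figures reproduce, and the formula's arithmetic is not in dispute here.

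**2. Where step 9 sits.** Steps 1 to 8 take their inputs from site lists, informant reports and information on movement between sites. Step 9 takes its input from a meeting. Step 10 is the use. Checking data quality is already the task of step 1 (completeness of lists, re-visiting a sample of sites that were not located), so step 9 cannot be read as only that check.

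**3. Is there a limit elsewhere?** Reading the section and the other places that mention stakeholders gives:

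| Possible safeguard | Found in the protocol? |
|---|---|
| Changes at step 9 limited to data or method errors | No |
| Pre-meeting estimate to be kept and reported | No |
| Definition of *reasonable*, or a plausible range | No |
| What follows if stakeholders object | No |
| Variance or interval for the PLACE estimate that could bound a change | No; the only variance formula in VIII.C is for the unique object multiplier |

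**4. Contrast within VIII.C.** The multiplier estimate has a formula, a variance and, under *Assumptions*, a duty to document and report where a stated assumption fails. It carries no acceptability condition.

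**5. Which outputs are exposed.** In Table 4, the first row is the size estimate itself, listed as the denominator belonging to PMP 1.1b. The *Test people* indicator (1.3b) divides by an estimated number living with HIV in the area, which presumably rests on the size estimate. Add the coverage and projection uses in VIII.C. Most other Table 4 indicators divide by people interviewed or tested, or by groups such as those diagnosed or on treatment, and do not depend on step 9.

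**6. Sensitivity (illustration only).** Coverage = R/N, with R people reached and N the accepted size. If the accepted size is f times the data-based size, coverage is multiplied by 1/f. Take N = 10,000 from the worked example and *assume* R = 3,000, since the protocol gives neither a number reached nor a size of change:

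| f | Accepted N | Coverage = 3,000/N | Factor 1/f |
|---|---|---|---|
| 1.00 | 10,000 | 30.0% | 1.00 |
| 0.90 | 9,000 | 33.3% | 1.11 |
| 0.80 | 8,000 | 37.5% | 1.25 |
| 0.70 | 7,000 | 42.9% | 1.43 |
| 0.50 | 5,000 | 60.0% | 2.00 |
| 1.25 | 12,500 | 24.0% | 0.80 |

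The last column does not depend on the assumed R. The table shows how coverage responds to the denominator; it says nothing about how likely a change is.

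**The case against.** The strongest reply is that step 9 describes a plausibility review in loose words. The method depends on informants' guesses, on formative research to allow for people who are missed, and on carrying percentages over to similar areas, so an outside check is sensible. Acceptance could come from explaining the method, from finding missed sites, or from not using a rejected figure; step 10 says only that the estimates may be used. The crude sum and the site map exist before the meeting (steps 4 and 5), cleaned data are archived and can be requested (VII.A), and dissemination needs the university's approval (X).

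Much of this stands, and it rules out several stronger readings that a reader might infer:

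- *That a disliked figure must be changed, or that every final figure passes by construction.* The text never says that the number is altered, or by whom, and it names two criteria rather than one.
- *That the figure would be pushed down to make coverage look better, or towards the earlier Luanda estimate of 2,200 female sex workers.* Nothing supports a direction. VIII.C also gives resource allocation as a use, which could favour larger figures, and nothing ties the review to the earlier estimate.
- *That the reviewers are the very bodies whose coverage is measured.* Step 9 does not define its stakeholders. The closing paragraph names users of the data; elsewhere (VI.C Step 1, and the readiness assessment in Appendix 1) the groups consulted are much broader and include key population representatives.

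What the reply does not remove is the condition itself. An archive and a crude sum are not a requirement to report the adjusted estimate as it stood before the meeting. Nor is this a detail that can be left to a statistical analysis plan: the protocol states the condition, and a plan that followed it would inherit it.

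**Conclusion.** The point holds as a matter of wording. Step 9 makes acceptability, together with an undefined reasonableness, a condition on the PLACE size estimate immediately before its use, and no provision confines changes to errors or preserves the pre-review figure. An untraced, result-dependent change is therefore permitted. The protocol does not predict one.

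No size of effect can be taken from the documents. The general relation is that coverage scales as 1/f; the percentages shown rest on an assumed 3,000 people reached and on the protocol's hypothetical 10,000. The exposure is confined to the size estimate itself, the indicators and coverage calculations that use it, and the projections. This is a cheap improvement, not a defect that undermines the study.

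**What to change.** Replace step 9 with text along these lines:

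> Record the data-based estimate from steps 1–8 before the meeting. Present it to stakeholders to check its plausibility and its inputs (missed sites, site counts, mobility assumptions). Change it only for documented input or method errors, by rerunning the affected steps. Report the pre-meeting estimate and, if it was corrected, the corrected estimate with reasons. Use the corrected data-based estimate in step 10, or the pre-meeting estimate if no error was found. If stakeholders adopt a different planning figure, report it separately as a consensus figure with its rationale.

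The meeting stays, genuine errors still get corrected before the figure is used, and no uncertainty range is demanded that steps 1 to 8 do not produce. The cost is the wording of one step and a line or two in the report. The downside is that the report may show a data-based figure beside a separate consensus figure, and the difference would have to be explained.

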### ***Population Size Estimation Analysis using Unique Object Multiplier and RDS***

We will collect information on the proportion of sex workers, MSM or transgender women who received a unique object. Three sets of results will be produced with the multiplier by comparing number of individuals receiving unique objects with 1) RDS numbers, 2) numbers from the distribution log from Data Source 1, and 3) numbers collected from survey interviews from Data Source 2.

**The formula for estimating the population size using a multiplier is**

$$N = \frac{(n_1 \times n_2)}{m}$$

where N is the estimate of total population size; n1 is the number of individuals receiving unique objects; n2 is the number of individuals participating in the RDS; m is the number in both populations (i.e. the number of MSM who received unique objects and participated in the RDS)

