##### ***Inclusion Criteria***

For the Cabinda study, female participants who meet the following eligibility criteria will be invited to participate in the project:

- At least one sexual contact for cash in the last 12 months
- At least 15 years of age at time of interview
- Resident of Cabinda province at time of interview
- Possession of a valid RDS coupon
- Consent to participate in a face-to-face structured behavioral survey

The interviewer will explain the study to the participant and ask for written informed consent (Appendix 9).

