#### ***Data Sources***

This method uses data from two overlapping sources to estimate population size. The first set of data comes from the number of unique objects distributed in a two week period by field staff two weeks preceding the implementation of the RDS survey. The second set of data comes from the RDS survey data, where study participants are asked whether they had received a unique object. The number of participants receiving a unique object is then multiplied by the inverse proportion of the percentage of RDS participants who received the unique object.

Source 1: Field staff distributing unique objects will report data regarding location and time of unique object distribution, and the exact number of unique objects distributed using the Population Size Estimation Form (Appendix 12).

Source 2: Relevant questions related to receipt of unique objects will be included in the RDS survey. These include:

1. Did you receive a [object] when contacted by a field staff in the past few months?
2. Can you show it to me?
3. Can you describe it to me? (if the [object] is described properly, show it to them)
4. Is this the [object] you received?
5. How many [objects] did you receive?
6. When did you receive this [object]?
7. Where did you receive this [object] (at what site)?

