## **Assumptions**

Members of the sex worker, MSM or transgender population must have a chance of being included in both sources of data. Data from both sources will be evaluated for any potential barriers to inclusion of members of the target population. Where this assumption is violated, this will be clearly documented and reported, and other sources of data will be considered.

The multiplier method requires clear and consistent population definitions, time reference periods, and catchment areas between the different data sources. During preparation for implementation of multiplier activities and collection of unique object and survey data, these issues will be carefully considered, and investigators will ensure that definitions across data sources will be coordinated.

**Objective 8: To provide data to inform and guide future behavioral surveys and prevention strategies targeting sex workers, MSM or transgender women in Angola.**

Responses collected at a roundtable meeting with key stakeholders held at the end of data collection will be analyzed. We will invite all USG agencies, local NGOs, and key government officials to discuss how survey results can assist ongoing and future behavioral activities targeting sex workers, MSM and transgender women and how these results can advance priorities outlined in the Country Operating Plan (COP) and Angola's National Strategic Plan (NSP). Priorities for Local AIDS Control Efforts (PLACE) studies in identifying high transmission HIV/AIDS areas to improve HIV prevention program delivery. Combined data from objectives A, B and C will be used to guide the design of new prevention messages targeting sex workers, MSM and transgender women. All results will be shared with NGOs and other agencies working directly with sex workers, MSM and transgender women in Angola.

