### Instructions for using Size Estimation Field Staff Contact Log

- 1. Date:** Write the date of distribution activity.
- 2. Distribution Site:** Write the site in which the distribution activity is taking place.
- 3. Time:** Write the time of distribution activity.
- 4. Age:** If the person is under 15 years old, do not give object or collect any other information.
- 5. Living or working in Cabinda Province:** Ask question: *Do you live or work in Cabinda province?* If answer is no, do not give object or collect any other information.
- 6. Is a female sex worker:** Ask question: *In the past 12 months, have you had received money for sex?* If answer is no, do not give object or collect any other information.
- 7. Have already received [object]:** Ask question: *Have you received a [object] by a field staff member in the past two weeks?*
- 8. Accepted [object]:** Explain that these objects are being distributed for a survey and that the only participation needed from him in this survey is to accept the object and that no other questions will be asked. If the person accepts the object, ask him to keep the object because in about two weeks to four months, someone might ask them again if they have received this object.

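### The Cabinda object multiplier uses the whole RDS sample as n2, including women who could not have received an object, and sets no reference date for N

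*Protocol*

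**What the plan says.** All references are to the protocol.

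- **Estimator** (VIII.C, unique object multiplier and RDS): N = n1 × n2 / m. The definitions are "n1 is the number of individuals receiving unique objects" and "n2 is the number of individuals participating in the RDS"; m is the overlap. The variance paragraph that follows also takes n2 as everyone interviewed.
- **Timing** (VI.F, Data Sources; Appendix 13, log instructions item 8): objects go out over two weeks before the RDS starts. Recipients are told that "in about two weeks to four months, someone might ask them again if they have received this object".
- **RDS eligibility** (VI.D, Inclusion Criteria): "Resident of Cabinda province at time of interview", plus at least one paid sexual contact in the previous 12 months. Neither criterion is tied to the distribution dates.
- **Object eligibility** (Appendix 13, log instructions items 5 and 6): living or working in Cabinda, and paid for sex in the past 12 months, both as of the hand-out.
- **Assumption** (VIII.C, Assumptions): population members "must have a chance of being included in both sources of data". Reference periods are to be consistent across sources, and violations are to be documented and reported.
- **Object count** (VI.F, Data Sources): Source 1 reports "the exact number of unique objects distributed using the Population Size Estimation Form". The survey asks "How many [objects] did you receive", but no rule says how the answer enters N.
- **Repeat receipt** (VI.F, Implementation; Appendix 13, item 7): one object per person. Staff ask about earlier receipt and give nothing if the answer is yes.

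**The concern.** The multiplier reads m/n2 as the share of the population that was reached by the objects. That reading needs every woman in n2 to have been reachable during distribution. The RDS criteria admit women who were not: those who came to Cabinda, or first sold sex, between the fortnight and the interview. Each lowers m/n2 and so raises N. The seven size-estimation questions listed in VI.F cover receipt, recognition, number, date and place of the object. None asks whether the woman was in Cabinda and in sex work when objects were given out, so the analyst cannot tell a late arrival from a woman who was missed.

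Cabinda's population size is a stated objective (section V), and size estimates are to serve as denominators for programme coverage (VIII.C). If N is too high by a factor 1/(1−a), coverage is too low by a factor (1−a). A larger RDS sample does not reduce this error, and the missing answer is hard to recover once interviews are done.

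**Working it through.** **Inputs from the protocol:** the formula N = n1 × n2 / m (VIII.C); n2 about 400 (VI.E); at least as many objects as the study sample size, so n1 = 400 is used (VI.F). The protocol gives no Cabinda population size or turnover rate, so there is no planned figure to reproduce.

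**Assumptions for illustration:** N1 = 1,000 women at distribution; a = share of the survey-time population that became eligible after distribution; l = share of the distribution-time population that left. The RDS is taken as representative of the survey-time population, and leaving as unrelated to holding an object.

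**Derivation.** Women who stay: N1(1−l). Survey-time population: N2 = N1(1−l)/(1−a). Object holders still present: n1(1−l). Hence

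m = n2 × n1(1−l) / N2 = n2 × n1 × (1−a) / N1

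N-hat = n1 × n2 / m = N1/(1−a), and N-hat/N2 = 1/(1−l).

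| a | l | N1 | N2 | m | N-hat | N-hat/N1 | N-hat/N2 |
|---|---|---|---|---|---|---|---|
| 0 | 0 | 1,000 | 1,000 | 160 | 1,000 | 1.000 | 1.000 |
| 10% | 0 | 1,000 | 1,111 | 144 | 1,111 | 1.111 | 1.000 |
| 20% | 0 | 1,000 | 1,250 | 128 | 1,250 | 1.250 | 1.000 |
| 0 | 20% | 1,000 | 800 | 160 | 1,000 | 1.000 | 1.250 |
| 10% | 10% | 1,000 | 1,000 | 144 | 1,111 | 1.111 | 1.111 |
| 20% | 20% | 1,000 | 1,000 | 128 | 1,250 | 1.250 | 1.250 |

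The ratios do not depend on N1; a run at N1 = 2,200 gave the same ones. Arrivals alone leave N-hat right for the survey date. Departures alone leave it right for the distribution date. With both, it is too high at either date.

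**With n2 restricted** to women eligible at distribution, n2 becomes 400(1−a) and m is unchanged:

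- a = 10%: 400 × 360 / 144 = 1,000
- a = 20%: 400 × 320 / 128 = 1,000

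This recovers the distribution-time population whatever l is. No survey item can do the same for the survey date, because women who left are not interviewed.

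**Objects against persons.** Suppose 400 objects are logged and holders took on average 1+d each, with d assumed and no turnover. Persons reached are 400/(1+d).

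- d = 5%: 381.0 persons, m = 400 × 381.0 / 1,000 = 152.4. Entering objects gives 400 × 400 / 152.4 = 1,050; entering persons gives 1,000.
- d = 10%: 363.6 persons, m = 145.5. Entering objects gives 1,100; entering persons gives 1,000.

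**The case against.** Four points deserve weight.

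1. **The protocol addresses consistency in general terms.** The Assumptions paragraph requires a chance of inclusion in both sources and coordinated reference periods, and promises to report violations. That is the right principle. However, the listed survey items cannot detect this violation, and the formula makes no adjustment for it.
2. **The Cabinda questionnaire (Appendix 5) is not shown.** It may already ask about length of residence or start of sex work. If so, no new question is needed, but the formula would still take all of n2.
3. **The gap may be short.** Distribution is placed just before the survey, and four months is the outer limit of a script read to recipients, not a planned average. Replacement of 20% or more in that time may be high. This limits the likely size of the bias, not its direction.
4. **Duplicates are screened.** A reader might infer that the estimator counts every object handed out. It does not: n1 is defined as individuals, each woman is to receive one object, and staff must refuse anyone who reports having one. VIII.C also plans a set of results based on the survey interviews. What stands is narrow: Source 1 is a tally of objects, the screen rests on self-report, and no rule says how the survey answer would correct the tally.

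A reader might also infer that late arrivals inflate N in every sense. The second and third rows of the table show otherwise: without departures, N-hat is correct for the survey date.

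**Conclusion.** The point holds in a limited form. With n2 as the whole RDS sample, N overstates the distribution-time population by 1/(1−a). It overstates the survey-time population as well only if women also left. Under equal replacement of 10% or 20%, the excess is 11% or 25% at both dates. These rates are assumptions, and the result also takes leaving to be unrelated to holding an object. The protocol does not say which date N refers to, so as written it cannot be judged which of these cases applies.

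The duplicate issue is secondary. A reader might multiply the two effects, for example 1.10/0.80 = 1.375, and report a 38% excess. The documents do not support that figure: both rates are assumed, and the protocol has a procedure meant to keep the second near zero.

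This is an inexpensive improvement worth making before interviews begin, not a flaw that invalidates the survey.

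**What to change.** 1. State in VIII.C that N refers to the distribution fortnight.
2. Unless the Cabinda questionnaire already has it, add one RDS item: at the distribution dates (to be named), did the woman live or work in Cabinda province, and had she received money for sex in the 12 months before? This mirrors the object eligibility in Appendix 13. It should not ask only about sex work in that fortnight, because that would drop women who were eligible for an object but inactive then.
3. Define n2 and m, in both the estimator and the variance paragraph, as women who answer yes.
4. Keep n1 as individuals. As a sensitivity analysis, divide the Source 1 count by the mean number of objects reported by women who received one, to correct for duplicates that pass the screen.

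**Cost:** one question, a few lines of text and a smaller n2. Treating n1 as fixed and sampling as binomial, the relative standard error of N is √((1−p)/m) with p = m/n2. At a = 10% this is √(0.6/144) = 6.5%, against √(0.6/160) = 6.1% had all 400 interviews been usable, so the interval is slightly wider than a full 400 would give. Against the unrestricted calculation on the same data, √(0.64/144) = 6.7%, nothing is lost, because the women removed are not in m. Object holders who wrongly answer no would reduce m a little.
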